**Blinding of participants, Personnel and Outcome assessors**

Only the outcome assessors will be blinded (open-label trial).

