**SECONDARY**

1. Proportion of patients with persisting anemic symptoms (weakness, easy fatigability) at two weeks after initial therapy.
2. Incidence of any maternal adverse events (such as diarrhea, nausea, vomiting and colitis) following commencement of therapy.
3. Incidence of any fetal adverse events (such as preterm labor or jaundice) following commencement of therapy.
4. Mean levels of renal function parameters (serum electrolyte, urea and creatinine) at two weeks after initial therapy.
5. Mean levels of liver function parameters (AST, ALT and ALP) and lipid profiles at two weeks after initial therapy.

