**Study design**

This will be an open-label randomized clinical trial.

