**Intervention Therapy**

## Standard doses of 50 mls of Mojeaga will be administered three time daily in conjunction with iron therapy Astyfer (Til Healthcare PVT Ltd, Andhra Pradesh, 517588 India) capsules two times a day (breakfast and dinner) for 2 weeks.

**Control Therapy**

Standard doses of one capsule of Astyfer will be administered alone two times a day (breakfast and dinner) for 2 weeks. These patients with confirmed diagnosis of anemia will be on conventional iron therapy administered without Mojeaga.

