**Follow-Up**

The trial is expected to last for at least 16 months. Recruitment will be within the first 6 months of commencement of the study and the follow up will be for at least 10 months from recruitment (ie total of 16 (6+10) months). All participants will be followed up in outpatient settings. During each follow-up weekly visit, patients will be contacted on phone on weekly basis to assess level of compliance. The patients will also be encouraged to record any side effects or adverse events in a paper that will be reviewed at each follow-up visit, and they will be explicitly asked about such events during each interview. The drug compliance will be checked before follow-up test. Any patient found to be developing complications such as worsening of the

symptoms from the study will be given appropriate treatment. Repeat hemoglobin level will be done 2 weeks post initiation of treatment in all the participants to confirm success of treatment (correction of anemia and levels of hemoglobin/hematocrit levels) and absence of adverse effects. All the pre and post (repeat) hemoglobin/hematocrit level will be carried out by hematologist: [name], while the LFT, Lipid profiles and SEUCR will be carried out by the Senior laboratory Scientist of Chemical Pathology- [name] in Nnamdi Azikiwe University Teaching Hospital, Nnewi laboratory.

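### The assessor blind is stated without limit, but it cannot protect the two outcomes that rest on the women's own reports: persisting symptoms and maternal adverse events

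*Combined protocol and SAP*

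**What the plan says.** The Study design section states: "This will be an open-label randomized clinical trial". The section on blinding adds only: "Only the outcome assessors will be blinded (open-label trial". It does not identify the assessors, list the outcomes they assess, or say how they are kept unaware of allocation.

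The arms differ visibly. Under Intervention Therapy, "50 mls of Mojeaga will be administered three time daily in conjunction with iron therapy Astyfer"; under Control Therapy, patients "will be on conventional iron therapy administered without Mojeaga". No dummy liquid is described.

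Two of the secondary outcomes are:
- outcome 1: "Proportion of patients with persisting anemic symptoms (weakness, easy fatigability) at two weeks after initial therapy";
- outcome 2: "Incidence of any maternal adverse events (such as diarrhea, nausea, vomiting and colitis) following commencement of therapy".

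They correspond to specific objectives 2 and 3. For adverse events, the Follow-Up section gives the source: patients are "encouraged to record any side effects or adverse events in a paper that will be reviewed at each follow-up visit", and they are also asked directly at each interview. The same section describes weekly phone contact about compliance and says: "The drug compliance will be checked before follow-up test". It assigns the blood tests to laboratory staff.

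The proforma records weakness, among other items, as present or absent under findings at clinical examination, before and after therapy.

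**The concern.** Blinding the person who writes down an answer does not blind the person who gives it. Fatigability is known only through the woman, weakness largely so, and the maternal adverse events are taken from her own record and her answers. She knows her arm. An unqualified statement that assessors are blinded could therefore lead a reader to credit these outcomes with a protection they do not have.

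The Statistical Analysis section would compare the proportions by chi-squared or Fisher's exact test at p ≤ 0.05 and express them as relative risks. Expectation in the Mojeaga arm could lower reported symptoms without any true effect. For adverse events the bias could go either way, because one arm alone takes the added product and may either report more about it or be more forgiving of it. The plan describes itself as a pilot that lays the ground for a full trial, so a misread symptom or tolerability result could carry forward.

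**Working it through.** **Outcome by outcome.** The question is whether blinding the assessor can work, given where the information comes from.

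| Outcome | Source in the plan | Can an assessor blind protect it? |
|---|---|---|
| Hematocrit, hemoglobin (primary) | Laboratory measurement (Follow-Up) | Yes |
| Renal, liver, lipid values | Laboratory measurement (Follow-Up) | Yes |
| Fetal or neonatal events | Proforma entries; assessor not stated | Yes, if judged by staff not told the allocation |
| Weakness, easy fatigability | The woman's own account; weakness ticked under clinical examination | No: the informant knows her arm |
| Maternal adverse events | The woman's paper record and direct questioning | No: the informant knows her arm |

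**Link with compliance.** The Follow-Up section describes adverse-event questioning together with compliance assessment and does not assign them to different people. An interviewer who handled both would learn the arm, because compliance with Mojeaga concerns only one arm. The documents do not say that one person does both.

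**Size, as an illustration.** The plan gives no figure to reproduce here. Inputs:
- Women per arm: 47 × (1 − 0.15) = 39.95, taken as 40 (Sample size determination).
- Significance: p ≤ 0.05 (Statistical Analysis), taken as two-sided, so 2.5% in Mojeaga's favour.
- Assumed: true persistence of 50% in both arms.
- Assumed: under-reporting in the Mojeaga arm of 5 to 20 percentage points.

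For a reporting shift d, with p1 = 0.50, p2 = 0.50 − d, p̄ = (p1 + p2)/2 and n = 40:

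P(significant in favour of Mojeaga) = Φ{[d − 1.96·√(2p̄(1 − p̄)/n)] / √[(p1(1 − p1) + p2(1 − p2))/n]}

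For d = 0.10: p̄ = 0.45; √(2 × 0.45 × 0.55/40) = 0.1112; √[(0.25 + 0.24)/40] = 0.1107; (0.10 − 1.96 × 0.1112)/0.1107 = −1.07; Φ(−1.07) = 0.14.

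Exact enumeration of the two binomials gives the values for the tests the plan names:

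| Reporting shift | Normal approximation | Chi-squared, uncorrected (exact) | Fisher (exact) |
|---|---|---|---|
| 5 points | 6.5% | 7.2% | 4.6% |
| 10 points | 14.3% | 15.5% | 10.7% |
| 15 points | 27.1% | 28.5% | 21.3% |
| 20 points | 44.6% | 45.8% | 36.8% |

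With no shift, the normal approximation gives 2.5%, the chi-squared test 2.8% and Fisher's test just under 2%. The calculation treats all 40 per arm as observed and does not apply the plan's rule that patients without an outcome count as treatment failures.

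**The case against.** The strongest defence is that nothing is concealed. The blinding sentence itself calls the trial open-label, the design section repeats it, and the documents never say that women's own reports are blinded. A separate assessor who is not told the allocation is compatible with the text, and the proforma carries a patient code number and no field for treatment arm. Only two secondary outcomes of a pilot are involved, relative risks with 95% confidence intervals are already planned, and nothing calls these results confirmatory.

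Much of this stands, and it limits the point. A reader might infer more than the documents support:

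- *That symptoms are asked about in the compliance contact.* No section says so. The proforma files weakness under clinical examination; only adverse-event questioning is described together with compliance.
- *That compliance is checked before symptoms or adverse events are elicited.* The sentence "The drug compliance will be checked before follow-up test" refers to a test, and the repeat tests described in that section are laboratory ones. It says nothing about the order of questions.
- *That an assessor blind is impossible.* A recorder could be kept unaware. The plan is silent on how, which is a gap. The woman's report would be unblinded all the same.
- *That only laboratory outcomes can be blinded.* Fetal outcomes such as preterm labor or jaundice can be assessed by a clinician who is not told the allocation.
- *That the percentages forecast this trial.* They rest on assumed rates and shifts. At 5 points the inflation is small.

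What the defence does not answer is that the sentence on blinding has no stated scope, and that a blinded recorder cannot remove bias from an unblinded informant.

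**Conclusion.** The point holds within narrow limits. The stated blinding does not protect secondary outcomes 1 and 2, and hence specific objectives 2 and 3, because women who know their arm supply the information. For adverse events, the plan also leaves open that one interviewer handles both the questions and the compliance check; that link is not documented for symptoms.

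The size cannot be derived from the documents. Under the stated assumptions a 10-point reporting shift alone gives about 11–15% significant results favouring Mojeaga, against a nominal 2.5%; larger shifts give more and a 5-point shift gives about 5–7%. The direction of bias for adverse events is unknown.

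It would be wrong to extend this to the primary outcomes. Hematocrit and the other laboratory values do not depend on what the women report. This is worth correcting because it changes what may be concluded about symptoms and tolerability, but it does not threaten the main comparison.

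**What to change.** 1. **Scope of the blind.** Restate the blinding section so that blinded assessment applies to the laboratory outcomes, with samples sent under code number, and to fetal and neonatal outcomes assessed by staff who are not told the allocation.
2. **Status of self-reported outcomes.** Declare persisting symptoms and maternal adverse events open-label. Report them with the relative risks and 95% confidence intervals already planned, as supportive results and not as blinded evidence of efficacy or tolerability.
3. **Recording.** Use the existing proforma checklist with the same wording in both arms, and complete it before compliance or study drug is discussed. Add rows for easy fatigability, diarrhea and colitis: all three are named in the secondary outcomes, but the form lists only epigastric pain, nausea, vomiting, dizziness, weakness and hematemesis.

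The cost is some wording in the blinding and analysis sections, three rows on the form and a fixed order of questions at existing contacts. No further patients, visits or tests are needed. The price in interpretation is that the symptom and tolerability results become supportive only.

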**Study Procedure/Drug Administration**

Patients with a clinical and laboratory diagnosis of anemia presenting in Outpatient Clinic or antenatal clinic of NAUTH Nnewi for symptoms or signs of anemia will be screened consecutively. All patients will also undergo routine medical examination including pulse rate, body weight, blood pressure determination and general examination to ascertain the presence of and severity of anemia. All consenting patients will be diagnosed to have either anemia or not after undergoing hematological test. Only patients with confirmed clinical and laboratory diagnosis of anemia will be randomized. Eligible patients will be sequentially allocated using an opaque sealed envelope to receive either Mojeaga and conventional oral Therapy, or the conventional oral iron Therapy alone. Therapies will be giving for two weeks**.**

**Intervention Therapy**

## Standard doses of 50 mls of Mojeaga will be administered three time daily in conjunction with iron therapy Astyfer (Til Healthcare PVT Ltd, Andhra Pradesh, 517588 India) capsules two times a day (breakfast and dinner) for 2 weeks.

**Control Therapy**

Standard doses of one capsule of Astyfer will be administered alone two times a day (breakfast and dinner) for 2 weeks. These patients with confirmed diagnosis of anemia will be on conventional iron therapy administered without Mojeaga.

**Follow-Up**

The trial is expected to last for at least 16 months. Recruitment will be within the first 6 months of commencement of the study and the follow up will be for at least 10 months from recruitment (ie total of 16 (6+10) months). All participants will be followed up in outpatient settings. During each follow-up weekly visit, patients will be contacted on phone on weekly basis to assess level of compliance. The patients will also be encouraged to record any side effects or adverse events in a paper that will be reviewed at each follow-up visit, and they will be explicitly asked about such events during each interview. The drug compliance will be checked before follow-up test. Any patient found to be developing complications such as worsening of the

symptoms from the study will be given appropriate treatment. Repeat hemoglobin level will be done 2 weeks post initiation of treatment in all the participants to confirm success of treatment (correction of anemia and levels of hemoglobin/hematocrit levels) and absence of adverse effects. All the pre and post (repeat) hemoglobin/hematocrit level will be carried out by hematologist: [name], while the LFT, Lipid profiles and SEUCR will be carried out by the Senior laboratory Scientist of Chemical Pathology- [name] in Nnamdi Azikiwe University Teaching Hospital, Nnewi laboratory.

**Sample size determination**

## Since this is a pilot study, we assumed a mean hematocrit level of 29.1% in the control group, mean hematocrit level of 31.5% in the intervention group after the intervention, 80% power, 95% confidence interval, standard deviation (SD) of 2.5, and a 15% dropout rate. Based on the assumptions, the minimum sample size required was 94 participants (47 in each arm). Furthermore, this sample size had 97% power to detect a change in hematocrit level from baseline (control: 6.5%; intervention: 10.5; SD: 3.8) between arms.

**Sampling Approach**

The randomized clinical trials are usually based on convenience sampling. After sampling, participants were randomly allocated to the intervention or control group (randomization) of the eligible, consenting women with diagnosis of anemia.

**Ethical consideration**

The study will adhere to CONSORT guidelines. The study protocol will be approved by the Nnamdi Azikiwe University Teaching Hospital, Nnewi, Nigeria ethics committee. The study has been registered and approved by the Pan African Clinical trial registry: at [**www.pactr.org**](http://www.pactr.org/). The approval number is **PACTR201901852059636 (see the approval enclosed).** The procedures to be followed will be in accordance with the guidelines of the World Medical Association’s Declaration of Helsinki (1964, and its later amendments). The drug (Mojeaga) is registered with NAFDAC Nigeria with registration number of **NRN: A7-0996L**. The nature of the study will be carefully explained to the patients and their informed consent will be obtained before being recruited into the study. The rights of the patients to participate or withdraw from the study will be fully honored without any adverse consequence to the patient.

**Beneficence to participants**

No patient will make any form of payment for participation in this study. The results obtained in this pilot study will show supposed benefits of Mojeaga based on the manufacturers’ claims and lay the framework for a full-blown trial on these preparations.

**Non maleficence to participants**

There is insufficient data (except those from the manufacturer) to guarantee absence of any undesired effect.

**Incentives to patients**

The cost of the research will be entirely borne by the investigators. The subjects and the investigators will not be paid. No payment will be made to the subjects.

**Certification of Analysis**:

To ensure a high quality standardized formulations, the raw material was authenticated and the product was laboratory tested and certified by [name] of Chemistry Department, University of Benin in accordance with Institute of Public analyst of Nigeria Decree no 100 of 1992 (see the certification enclosed).

**Funding:**

The research will partly be funded by the manufacturer of Mojeaga (Mojeaga International Ventures Ltd, Nigeria) and the researchers. The manufacturer will only be responsible for supplying the Mojeaga and Astyfer therapy to be used for the study. They will only supply drugs. The researchers will fund other expenses of the trial.

**NAME OF DOCTOR…………………………………………CODE NUMBER OF PATIENT……………………….…………….**

1. COMPUTER NUMBER OF PATIENT……………………………………… ...…..(2) GENDER………………………
2. DATE OF RECRUITMENT……………….... (4) TIME……………… (5) AGE……………...…………………

6.) Marital status : Married [ ] [single [ ] Divorced [ ](7.) LMP------------------ (8) GESTATIONAL AGE----------------

8. Parity…………….. 9. Body weight-------------- 9. Height: (cm)………………………………………………

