**OUTCOME MEASURES**

**PRIMARY**

1. Mean or median hematocrit level at two weeks after initial therapy.
2. Changes in the hematocrit level at two weeks after initial therapy.

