**Inclusion criteria**

Both obstetrics and puerperal adult patients with confirmed clinical and laboratory diagnosis of anemia (<10.0 g/dl) and with normal liver and renal function markers or profiles will be included.

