**Exclusion criteria**

- Pregnant women at first trimester of pregnancy (because of nausea and vomiting at this period).
- Multiple gestation
- Chronic medical disorders including HIV/AIDS, Cancers, etc.
- Women on chronic medications that cause anemia

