**19. SOME LABORATORY PARAMETERS**

| **LABORATORY VARIABLE** | **VALUES BEFORE THERAPY** | **VALUES AFTER THERAPY** | **NORMAL RANGES** |
| --- | --- | --- | --- |
| Na |  |  |  |
| K |  |  |  |
| Bicarbonate |  |  |  |
|  |  |  |  |
| AST |  |  |  |
| ALP |  |  |  |
| ALT |  |  |  |
|  |  |  |  |
| PCV/hematocrit |  |  |  |
| Hb |  |  |  |
| Wbc |  |  |  |
| Platelets |  |  |  |
|  |  |  |  |
|  |  |  |  |
|  |  |  |  |
|  |  |  |  |

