**FETAL/NEONATAL OUTCOME during therapy**

1. Preterm labour a.) YES—-b.) NO—-

2. Preterm PROM a.) YES—b.)NO-----

3. Birth weight (kg)----------------------------

4. birth anomaly

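### The form records neither pregnant/puerperal status nor a delivery date, so time since delivery cannot be used when the two-week hematocrit outcomes are analysed

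*Combined protocol and SAP*

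**What the plan says.** **Who may enter.** The Inclusion criteria admit "Both obstetrics and puerperal adult patients with confirmed clinical and laboratory diagnosis of anemia", with hemoglobin below 10.0 g/dl. The only exclusion tied to the timing of pregnancy is "Pregnant women at first trimester of pregnancy". No earliest or latest day after delivery is given, and the puerperium is not defined.

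**What is measured.** The second primary outcome is "Changes in the hematocrit level at two weeks after initial therapy". The first is the hematocrit level at the same time. The laboratory table on the form has a column "VALUES BEFORE THERAPY", so baseline hematocrit is collected.

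**What the form records.** Both copies of the proforma take "DATE OF RECRUITMENT" with a time, last menstrual period, "GESTATIONAL AGE" and parity. The block headed "FETAL/NEONATAL OUTCOME during therapy" asks about preterm labour, preterm rupture of membranes, birth weight and birth anomaly. Neither copy has an item for pregnant or puerperal status, a delivery date, or days since delivery.

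**How it is analysed.** Statistical Analysis names an independent t-test for continuous variables and no covariates. The randomisation section mentions no stratification by status.

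**The concern.** Gestational age places a pregnant woman in time. Nothing on the form does the same for a woman who has delivered. Two puerperal women at different points after birth are handled alike, although part of the two-week change in either may be recovery from the birth rather than response to treatment. Separating pregnant from puerperal women would not remove this spread within the puerperal group, and the form does not directly record even that split.

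Pregnant women are affected too. Late pregnancy is eligible, and the form itself provides for births during therapy. A woman who delivers between her two samples has a birth inside her change score, and the form cannot date it.

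What is at stake is precision, and the meaning of the change seen within each arm. The second matters because the section on beneficence presents this pilot as groundwork for a full trial. The designers of that trial would want to know how much of the variation in change comes from time since delivery.

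**Working it through.** **Inputs from Sample size determination.** Change outcome: 6.5 v 10.5, a difference of 4.0, SD 3.8, stated power 97%. Level outcome: 29.1 v 31.5, a difference of 2.4, SD 2.5. There are 47 women per arm with 15% dropout, so 47 × 0.85 ≈ 40 evaluable per arm. A two-sided 5% test is assumed, because the plan does not state sidedness.

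**The plan's own figure.** The normal approximation for a difference of 4.0 with SD 3.8 gives power of 99.7% at 40 per arm and 99.9% at 47 (t-based 99.6% and 99.9%). The stated 97% is not reproduced. That is a separate matter, and nothing below depends on it.

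**Assumptions, not in the documents.** Puerperal share *p* = 0.30 to 0.50. SD of the spontaneous two-week movement between puerperal women, by day of entry, *s* = 1.5 to 2.5 hematocrit points.

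**Variance due to the movement**, *p* × *s*²:
- low: 0.30 × 1.5² = 0.675
- high: 0.50 × 2.5² = 3.125

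**Relative to the planned variance** of 3.8² = 14.44:
- low: 0.675 / 14.44 = 4.7%
- high: 3.125 / 14.44 = 21.6%

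These are ceilings on what adjustment could recover. They would be reached only if the covariate captured all of the movement.

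**Effect on power if the movement comes on top of the planned SD** (40 per arm, t-based):

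| | Variance | SD | Power |
|---|---|---|---|
| Change, as planned | 14.44 | 3.80 | 99.6% |
| Change, low | 15.115 | 3.89 | 99.5% |
| Change, high | 17.565 | 4.19 | 98.8% |
| Level, as planned | 6.25 | 2.50 | 98.9% |
| Level, high | 9.375 | 3.06 | 93.3% |

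The change rows use the 4.0-point difference and the level rows the 2.4-point difference.

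**Chance imbalance between arms from the movement**, 1.96 × √(2*ps*²/40):
- low: 1.96 × √(2 × 0.675/40) = ±0.36 points
- high: 1.96 × √(2 × 3.125/40) = ±0.77 points

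The planned difference in change is 4.0 points.

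**Cost of adjusting.** With about 80 evaluable women the t-test has 78 residual degrees of freedom. Two extra terms cost roughly 2/78 = 2.6% and three cost 3/78 = 3.8%. At the low end of the assumed range, the precision gained from time since delivery alone is therefore close to break-even.

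**The case against.** The strongest objection is that little is lost. Study population and Study Procedure describe recruitment mainly through outpatient and antenatal clinics, and Follow-Up is in outpatient settings. Entry within hours of birth is not the main route, and the spread of entry days may be narrower than assumed above. The wording on women referred for treatment in the hospital leaves room for early entry, and no rule prevents it. That lowers the likely size of the effect but does not remove the gap.

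A delivery date might also be recovered. The form holds a hospital computer number, and last menstrual period plus gestational age would give the date if gestation at delivery had been entered. Both routes are possible, but the plan provides for neither and the form does not say which gestation is meant.

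A reader might infer three stronger things, none of which the documents support:
- *That the treatment comparison is biased.* Both arms are randomised concurrently, so the movement cancels in expectation.
- *That adjustment is worth up to 28% more women.* That figure, 1/(1 − 0.216) − 1 = 27.6%, needs the movement to lie wholly inside the planned 3.8² and the covariate to remove all of it, at the top of an assumed range. If the movement comes on top, the corresponding ceiling is 21.6%.
- *That the loss is beyond repair.* It cannot be modelled from the planned form data, but records may hold the date.

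**Conclusion.** The point holds as a modest gap in data collection and analysis. Time since delivery and pregnant/puerperal status are not recorded, so neither can be used as planned data for a primary outcome in a mixed population with no postpartum window. The consequence is some lost precision and within-arm change that is hard to read in puerperal women.

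Under the assumed shares and drift, the movement is at most about 5–22% of 3.8², and power for the 4.0-point change stays near 99%. Both the share and the drift are assumptions. That hematocrit is still moving after birth is general physiology, not a figure in the documents. The argument is stronger for change than for the two-week level. This is an inexpensive improvement rather than a threat to the trial's conclusion.

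**What to change.** 1. Add two items to the proforma: pregnant or puerperal at entry, and date of delivery. The date should also be completed when a delivery falls within the two weeks.
2. Prespecify a linear model for two-week hematocrit containing treatment, baseline hematocrit, pregnant/puerperal status at entry, and one term for days since delivery at entry, set to zero for pregnant women. A single term is preferable to several bands in a trial of this size.
3. Report deliveries during the two weeks by arm. They occur after randomisation, so use them to describe the data and not as a covariate in the main model.

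The cost is two form items and two or three degrees of freedom out of about 78 (two for status and days, three counting baseline hematocrit). Any earliest sampling time after delivery would affect eligibility and the start of therapy. It is for the investigators to decide and is not part of this change.
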